### Data Collection: Questionnaire

Interviewer-administered questionnaires will be used to collect data on demographic, lifestyle, and socioeconomic variables for the cases and controls. The questionnaire tool will comprise 2 parts: exposure information (part A) and sociodemographic information (part B). A life grid sheet will be used during interviews to efficiently collect retrospective information on lifestyle habits and other risk factors. To reduce observer bias, interviewers will not initially be informed about the aim of the research. Once cases are identified and interviewed, matching controls will be recruited and interviewed. Answers provided by participants will be converted to objective scores after data collection by the investigator (SC). The details on the parts of the questionnaire are as follows.

Exposure information (part A) will include (1) oral mucosal health status (whether white spots are present), (2) smoking habits, (3) type of products used, (4) e-cigarette smoking status (yes or no and current or previous), (5) age of onset, (6) duration of smoking, (7) pattern of smoking duration (continuous or intermittent), (8) frequency of smoking (daily, weekly, and occasionally), (9) number of cartridges (frequency), and (10) Tobacco consumption. Sociodemographic information (part B) will include (1) age, (2) sex, (3) occupation type, (4) education level, (5) income, and (6) ethnicity.

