### Recruitment Strategy

#### Overview

The recruitment strategy, targeting customers at e-cigarette stores and pedestrians, is strategically aligned with the study’s focus on e-cigarette users. The inclusion of community selection for matching controls, if quotas are not met, demonstrates flexibility in the recruitment approach. The disclosure of convenience and nonprobability sampling methods ensures transparency, thereby acknowledging the limitations inherent in these methods. A nuanced understanding of participant selection challenges is crucial for the accurate interpretation of study findings.

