### Sampling Methods

Convenience and nonprobability sampling methods will be used for the recruitment of cases and controls. The detailed sample size determination is shown in Multimedia Appendix 1 [16]. Briefly, the predefined power is 80% (*P*=.04), and the predefined proportions of the case and controlled groups are 11% and 2.5%, respectively. In all, 304 youths aged 15 to 24 years (n=152, 50% who smoke only e-cigarettes and n=152, 50% who do not smoke e-cigarettes or cigarettes) will be recruited.

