### Data Analysis

Descriptive statistics will be used for all binary, categorical, and continuous variables and expressed as tables, texts, and figures. Bivariate analysis will then be performed for relevant variables. The Shapiro-Wilks test will be performed for continuous variables to determine whether they follow the Gaussian distribution. Afterward, the independent 1-tailed *t* test and 1-way ANOVA will be used; otherwise, the Mann-Whitney *U* test and Kruskal-Wallis test will be performed. For cross-tabulation of 2 categorical variables, the chi-square test will be used. Variables that do not fulfill the assumption of this test will be analyzed using Fisher exact test. Comparisons with *P*=20 will be used to implement multivariable analysis using multiple logistic regression. Odds ratios and 95% CIs will be determined for e-cigarette smoking and other individual factors. For all analyses, *P*<.05 will be used to denote statistical significance. Statistical analyses will be performed using the SPSS (version 27; IBM Corp).

The control and e-cigarette groups will be subjected to a *t* test (assuming the data meet the normality criteria and do not meet the criteria for the rank sum test) to verify whether e-cigarettes cause harm.

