## Discussion

In examining the potential negative impact of e-cigarettes on the oral mucosa, this study deliberately focused its investigation on this specific aspect, excluding other potential confounding factors that might influence the results. Notably, variables such as alcohol consumption, daily routines, and gender differences were not considered in the experimental design. While these factors were omitted from this study, they were duly documented in the questionnaire phase, laying the groundwork for future investigations to delve into these variables. This strategic choice aimed to isolate the primary relationship between e-cigarette use and oral mucosal health, with the intention to refine and expand the scope in subsequent research endeavors.

The findings of this study align with existing literature on e-cigarettes, which suggests a correlation between the chemicals present in e-cigarettes and cytotoxicity, leading to damage to the oral mucosa. This corroborates with prior research, providing further evidence of the potential harm associated with e-cigarette use [10,16,17]. The recognition of this association holds significant implications for public health, emphasizing the need for awareness campaigns and regulatory measures to mitigate the adverse effects on oral health. Moreover, the study acknowledges the diverse landscape of e-cigarettes in the United States, encompassing various brands and flavors, each containing distinct chemical compositions. Given this complexity, it is acknowledged that the study does not comprehensively analyze all individual chemicals present in different e-cigarettes. This limitation prompts a call for future experiments to undertake a more nuanced examination of the diverse chemical profiles within e-cigarettes to better understand their distinct impacts on oral mucosal tissues.

Despite the valuable insights provided by this study, certain limitations should be acknowledged. The decision to exclude factors such as alcohol consumption and daily routines may have implications for the generalizability of the findings. In addition, the complexity of e-cigarette compositions poses a challenge, as the study did not extensively investigate the myriad chemicals present in different e-cigarette products. Future research endeavors should consider a more comprehensive approach, encompassing a broader range of variables and a detailed analysis of the chemical constituents of various e-cigarettes.

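### Controls are called matching, but no matching factor is named and the analysis neither uses matching nor guarantees adjustment for age and sex

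*Protocol article*

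**What the plan says.** **Matching is announced twice.** Data Collection: Questionnaire states: "Once cases are identified and interviewed, matching controls will be recruited and interviewed". The Overview under Recruitment Strategy refers to it again: "The inclusion of community selection for matching controls, if quotas are not met". Neither place gives a factor, a ratio, or the type of matching.

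**Sampling is by convenience.** Sampling Methods: "Convenience and nonprobability sampling methods will be used for the recruitment of cases and controls". The e-cigarette group comes largely from e-cigarette stores. The other sources are pedestrians and, if quotas are short, community settings. The planned size is 152 per group, with assumed lesion proportions of 11% and 2.5%.

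**The analysis is unpaired throughout.** For continuous variables, "the independent 1-tailed *t* test and 1-way ANOVA will be used"; "otherwise, the Mann-Whitney *U* test and Kruskal-Wallis test will be performed". Categorical variables get chi-square or Fisher exact tests. Comparisons that pass a P threshold (printed as P=20, which I take to mean .20) "will be used to implement multivariable analysis using multiple logistic regression". The section closes with a two-group t test as the check on whether e-cigarettes do harm.

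**Sex is set aside in the design.** Study Population recruits irrespective of sex, race, occupation and socioeconomic status. The Discussion says that "gender differences were not considered in the experimental design". Age and sex are nevertheless recorded in part B of the questionnaire.

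**The concern.** Seeking controls after the cases have been interviewed, and calling them matching, suggests that they are chosen to resemble the cases on something the interview recorded. If so, that factor belongs in the analysis, through pairing or as a model term. The Data Analysis section does neither.

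If nothing is matched, the word suggests a comparability that the design does not provide. Store customers and pedestrians aged 15 to 24 may differ in age and sex, and the t test offered as the check on harm has no adjustment. The regression does not reliably close the gap, because age and sex enter only if they pass a screen.

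**Working it through.** **Inputs from the article (Sampling Methods).** p1 = 0.11, p0 = 0.025, n = 152 per group. The within-pair correlation ρ is not given. I assume 0.1 to 0.3 and also look at weak matching.

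**1. Does the sample size show which design is meant?** For two independent proportions, 80% power, two-sided:

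| Method | n per group, α = 0.05 | n per group, α = 0.04 |
|---|---|---|
| Pooled normal approximation | 136 | 145 |
| Same, continuity-corrected | 159 | 168 |
| Fisher exact | 148 | 156 |

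The stated 152 lies between the two Fisher figures; its Fisher power is 81.5% at 0.05 and 78.9% at 0.04. An unpaired calculation therefore reproduces it to within 3%. So does a McNemar calculation with ρ = 0 and α = 0.04 (148 pairs). 136/0.90 = 151.1, rounded up to 152, also fits, although the article states no dropout. The sample size shows no allowance for matching, but it does not settle the question.

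**2. If controls are pair-matched 1:1.**
- v1 = 0.11 × 0.89 = 0.0979; v0 = 0.025 × 0.975 = 0.0244; sum = 0.1223; √(v1·v0) = 0.0489.
- Paired variance of the difference, per pair: 0.1223 − 2ρ × 0.0489.
- Independent 95% half-width: 1.96 × √(0.1223/152) = 5.56 percentage points.

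| ρ (assumed) | Paired variance | Unpaired SE / paired SE | Paired 95% half-width (points) |
|---|---|---|---|
| 0 | 0.1223 | 1.00 | 5.56 |
| 0.1 | 0.1125 | 1.04 | 5.33 |
| 0.2 | 0.1027 | 1.09 | 5.10 |
| 0.3 | 0.0930 | 1.15 | 4.85 |

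The unpaired interval is too wide, not too narrow.

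A simulation gives the weak-matching case: 20,000 runs, 152 pairs matched on one binary factor of 40% prevalence, factor-outcome odds ratio 1, 3 or 6 (all assumed). The paired/unpaired SE ratio was 0.98 to 1.00, coverage of the unpaired interval 94.4% to 95.1%, and unpaired type I error 4.5% to 4.6% at a nominal 5%.

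**3. If controls are frequency-matched.** Ordinary logistic regression is suitable when the matching factors are in the model. The plan lets the screen decide. If the screen compares the groups, a well-matched factor shows little difference and tends to be left out. If it compares lesion status, there are few events to work with: 152 × 0.11 + 152 × 0.025 = 16.7 + 3.8 = 20.5, about 21. Because the groups are formed on exposure, leaving out a factor that really is balanced costs little. Any imbalance left by convenience recruitment, however, goes unadjusted.

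**4. If controls are not matched.** The t test compares two convenience samples with no control of age or sex. No size can be given, because the article states neither the age and sex make-up of the sources nor how lesions vary with them.

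**The case against.** The strongest reply is that pair matching is never stated. Recruitment is described in terms of quotas, which is group-level language, and the community route takes controls who meet the study criteria; that may be all that *matching* means. The analysis would then be right to be unpaired. Details of matching are also commonly left to a fuller protocol or analysis plan. Age and sex are collected and can enter the regression, and any loss under pairing is small and conservative.

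Most of this stands, and it rules out four stronger readings that a reader might infer:
- *The intervals are invalid.* Not supported. Under pairing they are mildly too wide; under the other readings the unpaired form is acceptable in itself.
- *The odds ratio is pulled towards 1.* That bias arises when matching is on outcome status. Study Design does use the case-control label, but the selection criteria form the groups by e-cigarette use. With ρ = 0.1, the pair-conditional odds ratio is (0.10725 − 0.00489)/(0.02225 − 0.00489) = 5.89, against a marginal (0.11/0.89)/(0.025/0.975) = 4.82. These are different estimands, not a bias.
- *Readers are told that age and sex are balanced.* The article does not say this.
- *Matching on sex contradicts the Discussion.* Sex is never named as a matching factor, and Study Population and Discussion agree with each other.

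The reply does not remove the mismatch. The article does not merely omit detail. It announces matching and then fixes methods that make no use of it, with a screen that can drop any matching factor or confounder. Under the reply's own unmatched reading, the unadjusted t test remains.

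**Conclusion.** The point holds as an inconsistency between the stated design and the stated analysis, and it should be settled before recruitment. It is not a failure of validity. The 4% to 15% excess width under 1:1 pairing rests on assumed correlations of 0.1 to 0.3, for which the article gives no source; with weak matching the excess is close to zero. The more consequential branch is the unmatched one, where confounding by age and sex in the t test is uncontrolled and its size cannot be stated from the document. Under frequency matching, the defect is that adjustment is left to a screen.

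**What to change.** 1. Make the primary comparison a logistic regression of lesion presence on e-cigarette group, with age (continuous, to spare parameters) and sex forced in whatever the P screen shows. This replaces the unadjusted t test as the main evidence.
2. Choose one description of the controls. Either name the matching factors, ratio and type, and force those factors into the model as well (conditional logistic regression if pairs are formed), or delete *matching* in both places and state that the groups are unmatched.
3. Bring Study Population and Discussion into line with that choice. The Discussion should say whether sex is handled in the design, in the analysis, or in neither.

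Cost: wording only, since no participant has been recruited and both variables are already in part B. Age and sex add two parameters, or three if one further matching factor is named, against about 21 expected events. With group, age and sex in the model that is 20.5/3, or about 7 events per parameter. The interval will be slightly wider; a penalised fit can be used if estimates are unstable.

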**Methods:**

In this prospective study, 304 youths aged 15 to 24 years (n=152, 50% who smoke only e-cigarettes and n=152, 50% who do not smoke e-cigarettes or cigarettes) will be divided into 2 groups for a controlled study. Whether e-cigarettes cause oral mucosal lesions will be verified by comparing the odds of oral mucosal lesions in the 2 experimental groups. For this experiment, the predefined power is 80% (*P*=.04), and the predefined proportions of groups 1 and 2 are 11% and 2.5%, respectively.

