**Conclusions:**

e-Cigarettes are still an unfamiliar topic to the public, and it is still unknown whether they can cause damage to the oral mucosa. This experiment aims to find out whether there is a link between the 2. There are still many limitations in this study, such as the lack of categorization of e-cigarettes and the lack of testing methods for oral mucosal status. These limitations are expected to be addressed in the future as the experiment is formally conducted and further optimized.

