### Hypothesis

This study hypothesizes that e-cigarettes, in the speculated absence of tobacco, may still induce carcinogenesis. Alternatively, it is suggested that this habit may trigger an imbalance in the oral microbiome that predisposes the mucosal epithelium to oral cavity cancer with other etiological factors. This presupposed risk is likely proportional to the frequency and duration of e-cigarette smoking. The oral mucosal health of participants will be determined by determining the presence of white spots in the mouth (the main feature of the oral mucosa that is damaged by smoking behavior).

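### The only outcome described is a questionnaire item on white spots, but the claims are about mucosal lesions, damage and malignant potential, and the 80% power is conditional on how accurate that item is

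*Protocol article*

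**What the plan says.** **How the outcome is obtained.** Data Collection: Questionnaire names the instrument: "Interviewer-administered questionnaires will be used to collect data on demographic, lifestyle, and socioeconomic variables for the cases and controls". Item 1 of part A, under exposure information, is "oral mucosal health status (whether white spots are present". On scoring it says: "Answers provided by participants will be converted to objective scores after data collection by the investigator". No examination, examiner or diagnostic criterion appears anywhere in the article.

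**How the outcome is defined.** Hypothesis says "The oral mucosal health of participants will be determined by determining the presence of white spots in the mouth" and justifies white spots as "the main feature of the oral mucosa that is damaged by smoking behavior". It names no assessor. The abstract's Conclusions list "the lack of testing methods for oral mucosal status" as a limitation to be dealt with later.

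**What is claimed.** The abstract's Methods state: "Whether e-cigarettes cause oral mucosal lesions will be verified by comparing the odds of oral mucosal lesions in the 2 experimental groups". The abstract's Objective is to find out whether e-cigarettes damage the mucosa, and Primary Outcome speaks of mucosal conditions in general. Research Significance expects evidence of malignant potential, or else the exclusion of e-cigarettes as a cause of oral cancer.

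**Power.** Sampling Methods gives 80% power (P=.04), proportions of 11% and 2.5%, and 152 per group, and refers to an appendix for detail. Data Analysis uses P<.05.

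**The concern.** What is recorded and what is to be concluded are different things. An answer about white spots is an imperfect indicator of a mucosal lesion, and says less still about cancer risk.

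With a control rate as low as 2.5%, specificity matters most. A false-positive rate of one or two per cent is of the same order as the true rate, so a large share of positive answers in controls would be wrong. Error that is equal in both groups pulls the odds ratio towards 1 and lowers power. Error that differs between groups can create an association. That is plausible here: users know their exposure, may be recruited in e-cigarette stores, and answer the outcome item in the same interview as the exposure items.

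In either case the result would be reported as a finding about lesions. A null result could even be read as clearing e-cigarettes of carcinogenic potential.

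**Working it through.** **Inputs from the protocol article:** 152 per group; proportions 0.11 and 0.025; P=.04, read as a two-sided significance level (sidedness is not stated); P<.05 in Data Analysis. **Assumed, because the article gives no values:** sensitivity (Se) and specificity (Sp) of the white-spot item.

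**Step 1: the plan's own figure.** The true odds ratio is (0.11 × 0.975)/(0.025 × 0.89) = 4.82. Power at 152 per group, two-sided 0.04, with no outcome error:
- pooled two-proportion formula: 81.9%
- exact power of the uncorrected chi-square test, by enumeration: 85.3%
- exact power of Fisher's test: 78.9%

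The stated 80% is therefore reasonable for an outcome measured without error.

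**Step 2: equal error in both groups.** The expected observed proportion is q = Se × p + (1 − Sp) × (1 − p). Example with Se 0.9, Sp 0.98:
- users: 0.9 × 0.11 + 0.02 × 0.89 = 0.1168
- controls: 0.9 × 0.025 + 0.02 × 0.975 = 0.0420
- odds ratio: (0.1168 × 0.958)/(0.042 × 0.8832) = 3.02
- share of positive answers in controls that are true: 0.0225/0.042 = 54%

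Exact chi-square power at 152 per group:

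| Se | Sp | Users | Controls | Odds ratio | Two-sided 0.04 | Two-sided 0.05 |
|---|---|---|---|---|---|---|
| 1 | 1 | 11.0% | 2.5% | 4.82 | 85.3% | 87.0% |
| 0.9 | 1 | 9.9% | 2.25% | 4.77 | 81.1% | 83.0% |
| 1 | 0.99 | 11.9% | 3.5% | 3.75 | 78.1% | 80.7% |
| 0.9 | 0.99 | 10.8% | 3.2% | 3.63 | 72.6% | 75.3% |
| 0.9 | 0.98 | 11.7% | 4.2% | 3.02 | 65.0% | 68.7% |
| 0.8 | 0.97 | 11.5% | 4.9% | 2.50 | 51.0% | 55.2% |
| 0.8 | 0.95 | 13.3% | 6.9% | 2.07 | 41.6% | 46.0% |

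Losing some sensitivity alone costs little. Losing specificity does most of the damage.

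**Step 3: unequal error, no true effect.** Take a true rate of 2.5% in both groups, Se 0.9, and Sp 0.95 in users v 0.99 in controls:
- users: 0.0225 + 0.05 × 0.975 = 0.07125
- controls: 0.0225 + 0.01 × 0.975 = 0.03225
- apparent odds ratio: (0.07125 × 0.96775)/(0.03225 × 0.92875) = 2.30
- chance of rejection at two-sided 0.05: 33% by exact chi-square (24% by Fisher's test)

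**The case against.** **The power loss rests on assumptions.** This stands. No sensitivity or specificity is given, and 0.95 is a demanding low end: it raises the expected control rate from 2.5% to 6.9%. The sample size appendix is not available, so 11% and 2.5% may already be rates of reported white spots, in which case the error is built in. A reader might infer that the 80% is simply wrong. The documents do not support that. Se 0.9 with perfect specificity still gives 81%, and at the 0.05 level perfect sensitivity with Sp 0.99 gives 80.7%. A one-sided 0.05 test would also soften the loss (pooled formula: 82.9% at Se 0.9/Sp 0.99, 58.1% at 0.8/0.95), but Data Analysis attaches its 1-tailed wording to the t test only.

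**An examination may exist in a fuller document.** A reader might infer that nobody will look in the mouth. The article does not say so. It says only that answers are scored, and it concedes that testing methods are lacking. The supportable statement is that no examination is described.

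**The limitation is disclosed.** In part. It is wrong to say that it reaches no conclusion, since it stands in the abstract's Conclusions. It is absent from the Discussion's limitations and from its closing paragraph.

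**White spots are a declared marker.** True. Hypothesis says so and gives a reason, so using one sign is a disclosed choice and not in itself a contradiction. It does not justify conclusions on damage or carcinogenic potential.

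**There are safeguards.** Interviewers are initially kept unaware of the aim, and an expert panel will judge face and content validity. Neither measures how accurate the white-spot item is. Cronbach's alpha is planned for the exposure scales only.

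**Conclusion.** The point holds in two parts.

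First, the claims go beyond the outcome described. This rests on the text alone and needs no assumption: a questionnaire item on white spots cannot carry conclusions on lesions, damage or malignant potential, and cannot exclude e-cigarettes as a cause of cancer.

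Second, the 80% power is conditional. It stands if 11% and 2.5% are reported proportions, or if specificity is essentially perfect and sensitivity is about 0.9 or better. If they are true lesion rates, assumed false-positive rates of 1% to 5% with sensitivity 0.9 to 0.8 bring the odds ratio to about 3.6 to 2.1 and power to about 73% to 42% at two-sided 0.04 (75% to 46% at 0.05). Unequal specificity of the assumed size gives an apparent odds ratio of about 2.3 from nothing. These figures show how sensitive the design is to outcome error. They do not estimate the error this questionnaire will have.

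**What to change.** 1. In the abstract's Objective and Methods and in Primary Outcome, name the outcome as white spots recorded by questionnaire. Limit the conclusions to that, and remove from Research Significance the claim to show or exclude carcinogenic potential. Carry the admitted measurement limitation into the Discussion's limitations and its closing paragraph.
2. In Sampling Methods, state whether 11% and 2.5% are reported or true proportions, and make the 80% power conditional on the answer. If they are true proportions, show power over a range of sensitivity and specificity.
3. Add a quantitative bias analysis of the odds ratio, under equal and unequal sensitivity and specificity by group, with the ranges fixed before data collection.

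The cost is narrower conclusions, a less favourable power statement and one extra analysis. No participants or study visits are added. The article reports that no data have been collected, so all of this can still be set in advance. The changes make the claims match the measurement; they do not make the measurement more accurate.

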**Objective:**

This aims to determine whether e-cigarettes cause damage to the oral mucosa. This study also aims to evaluate the association between e-cigarette smoking and oral mucous membrane lesions in young adults. The objectives are to (1) compare the oral mucosal conditions in participants with and without e-cigarette smoking habits, (2) assess the effect of the amount of e-cigarette smoking on oral mucosal conditions, and (3) assess the effect of the duration of e-cigarette smoking on oral mucosal conditions.

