## Introduction

### Background

Oral cavity cancer is the most prevalent head and neck malignancy worldwide [1,2]. This malignant phenotype is often associated with habitual and lifestyle factors, such as tobacco smoking, excessive alcohol consumption, betel nut chewing, and low intake of fruits and vegetables [1]. Due to restrictive government policies and proven negative health effects in many parts of the world, the use of tobacco has declined in recent decades [3]. Electronic cigarettes (e-cigarettes) were invented by a Chinese pharmacist, Hon Lik, in 2003, who envisioned that they would replace conventional cigarettes due to their deleterious effects [4]. e-Cigarette companies claim that handheld devices can provide smokers with the same experience as conventional cigarettes while reducing their negative effects. e-Cigarettes were introduced with the hope that the smoking population would gradually stop using conventional cigarettes and switch to e-cigarettes. With the waning consumption of regular cigarettes, the use of e-cigarettes has surged worldwide, indicating that smokers now consider e-cigarettes viable replacements. Moreover, recent data have indicated that e-cigarette smoking practices are more common among teenagers and young adults [5,6]. However, most people do not take this soaring statistic seriously and allow young people to use e-cigarettes freely. Most people believe that the health hazards of smoking only manifest with increasing age and, thus, concern is unnecessary regarding the use of e-cigarettes by young people.

It is no surprise that young adults are the primary habitual e-cigarette users. The portability of the devices, different flavors with less nicotine, and convenient use of e-cigarettes make them appealing to young people. Data from the 2011-2018 National Youth Tobacco Survey in the United States demonstrated that e-cigarette use among high school students increased from 1.5% in 2011 to 20.8% in 2018 [3]. In 2022, the Centers for Disease Control and Prevention indicated that 2.55 million US middle and high school students reported current (past 30 days) e-cigarette use; nearly 85% of these young people used flavored e-cigarettes, and more than half used disposable e-cigarettes [7]. This increase has also become noticeable in community settings. Unfortunately, adults do not pay enough attention to the use of e-cigarettes, especially in schools.

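### The only quantity question counts cartridges, a unit that does not fit disposables, so Objective 2 (amount of use) has only a coarse frequency category for disposable users

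*Protocol article*

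**What the plan says.** The Objective paragraph of the Abstract lists three aims. The second is to "assess the effect of the amount of e-cigarette smoking on oral mucosal conditions"; the third concerns duration, so amount is meant as something separate from duration.

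The section Data Collection: Questionnaire lists the exposure items of Part A. Those bearing on use are:
- product type ("3) type of products used");
- age of onset, duration, and continuous or intermittent pattern (items 5 to 7);
- a three-level frequency ("8) frequency of smoking (daily, weekly, and occasionally");
- one count ("9) number of cartridges (frequency").

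No unit is given for disposable or refillable devices, and the list does not say which item or score represents amount.

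The Background section reports for 2022 that "2.55 million US middle and high school students reported current (past 30 days) e-cigarette use", and of these young people that "more than half used disposable e-cigarettes". The eligibility sections set no limit on device type.

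The Hypothesis section frames dose differently: "This presupposed risk is likely proportional to the frequency and duration of e-cigarette smoking".

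**The concern.** A dose-response aim needs a dose that means the same thing for every user. A cartridge count can serve for someone who replaces cartridges. A person who uses sealed disposables has no obvious answer: they might say none, leave the item blank, or count devices as if they were cartridges, and interviewers might handle it differently from one another. The article's own background suggests that such users could be common.

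The frequency item applies to every device, but it records how often and not how much, and it puts all daily users in one class. Users must have vaped over the last 210 days, and one recruitment channel is e-cigarette stores, so daily users may well be numerous. Differences in amount among them would then be invisible for anyone on a disposable.

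At stake is a named secondary aim. If the item is blank for disposables, Objective 2 is answered on a subset with fewer lesions. If it is entered as zero, heavy users fall to the bottom of the scale and a real gradient is flattened. If it is dropped in favour of frequency, the analysis becomes one of frequency and not of amount.

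**Working it through.** The plan gives no figure for Objective 2, so there is none to reproduce. The check sets the sections side by side and then sizes the affected share.

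**Does any item measure quantity for a disposable user?**

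| Part A item | Applies to disposables? | Measures how much? |
|---|---|---|
| 3, product type | yes | no; allows stratification only |
| 5 to 7, onset, duration, pattern | yes | no; duration is Objective 3 |
| 8, frequency in three levels | yes | only coarsely; one class for all daily users |
| 9, number of cartridges | unit does not fit | yes, for cartridge users |

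That the unit does not fit rests on the ordinary meaning of the words; the article defines neither cartridge nor disposable.

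**How many users and lesions?** Inputs: N = 152 users and a proportion of 11% (Sampling Methods), read as the lesion proportion among users. The share on disposables, d, is an assumption because the article does not give it for this sample.

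- All users: 152 × 0.11 = 16.7 expected lesions.
- Without a literal cartridge count: 152 × d users.
- With one: 152 × (1 − d) users and 152 × (1 − d) × 0.11 lesions.

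| d (assumed) | Users on disposables | Users with a cartridge count | Expected lesions among the latter |
|---|---|---|---|
| 25% | 38 | 114 | 12.5 |
| 50% | 76 | 76 | 8.4 |
| 60% | 91 | 61 | 6.7 |

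**What could this do to the amount analysis?** This part is illustrative only. Logistic simulation with 152 users, 11% lesions, log-normal amount (SD 0.8 on the log scale), 50% disposables unrelated to amount, a true odds ratio of 2.0 per SD of amount, and two-sided P<.05:

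| How amount is handled | Power, risk follows log amount | Power, risk follows raw amount |
|---|---|---|
| Device-neutral, error-free | about 70% | about 85% |
| Cartridge users only | about 40% | about 57% |
| Disposables entered as 0 | about 25% | about 45% |
| Three-level frequency alone (assumed 50/25/25 split, perfectly ordered) | about 45% or a little more | about 33% |

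With cartridge users only, the estimated odds ratio stays near 2.0. With disposables entered as zero it falls to about 1.3 (log scale) or 1.5 (raw scale). The levels move a good deal with the exposure scale, but in every case the device-neutral measure does best. The effect size, spread, device mix, frequency split and coding rules are all assumptions.

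**The case against.** The strongest reply is that the questionnaire does measure exposure for everyone. Duration, pattern and frequency apply to any device, product type is recorded, and the Hypothesis section names frequency and duration as the dose. This stands. A reader might infer that Objective 2 has no valid exposure measure at all, or that the proportionality hypothesis goes untested; the document supports neither. A coarse measure is not an invalid one, and the two dose components named in the hypothesis are both collected.

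Three further points also stand:
- No section says that disposables are coded as zero or missing. A reader might infer that heavy disposable users will be recorded as non-consumers, but that is one possible outcome and not a written rule. An interviewer could count a finished disposable as one unit.
- A reader might infer that about half of this study's users are affected. The Background figure describes middle and high school students, whereas this is a convenience sample aged 15 to 24 recruited at stores and from pedestrians.
- The Discussion's remark that brands and flavors differ concerns chemical composition, so it says nothing about whether cartridges hold comparable volumes.

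It can also be said that the article condenses a fuller questionnaire, and that expert and lay review of face and content validity is planned before use. Different wording for disposables cannot be ruled out, and the review might catch the mismatch. But the article does name the unit, and that unit sits badly with its own background. The only numeric reliability criterion is Cronbach α, which does not test whether a unit is comparable across devices. Conversion of answers to scores after data collection cannot recover an amount that was never asked.

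Lastly, the simulated benchmark is free of error. Adding assumed recall error (SD 0.5 on the log scale) to the device-neutral measure lowers its power from about 85% to about 69% on the raw scale. That narrows the advantage without removing it.

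**Conclusion.** The point holds as a mismatch between Objective 2 and the one quantity item meant to serve it. For users of disposables, only a three-level frequency would remain as a measure of how much they use, so the amount analysis would be misclassified, incomplete or coarse for them.

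The size depends on a device mix that the article does not give. At an assumed 50%, about 76 of 152 users and about 8 of about 17 expected lesions are involved; at 25%, 38 users and about 4 lesions (16.7 − 12.5 = 4.2). The power figures show direction only.

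The comparison of users with non-users does not use item 9 and is unaffected, as is the frequency-and-duration hypothesis. This is a change that should be made for a named secondary aim. It is not a fault in the main analysis.

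**What to change.** Replace item 9 with a device-neutral amount asked of every user. Take the device type from item 3 (disposable, prefilled cartridge, refillable). Then ask either days used per week and sessions or puffs per day, or units finished per week with the labelled liquid volume. State in the protocol which of these is the amount for Objective 2, and keep the three-level frequency as a separate descriptor. Ask the planned validity panel to confirm that the item can be answered for each device type.

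The cost is two or three more questions in an interviewer-administered form, a slightly longer interview, and some recall error in self-reported puffs or volume. The questionnaire has not been fielded and the Results section says no data exist, so the change is cheap now; after fieldwork the missing information could not be restored.
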